### Goals of the intervention

Both the MI and SDI women were given intervention goals according to their baseline BMI as shown in Additional file 1. Women found to be in the healthy weight range (18.5 – 24.9 kg/m^2^) at baseline were advised to maintain that weight within 1 kg for the duration of the study. Written advice was provided in booklet format so the women could meet their Recommended Dietary Intakes (RDI) for micronutrients and macronutrients [29] and an intake of 8300 kJ/day, which is the estimated requirement for women 51–70 years with a mean height of 1.6 m and an activity factor of 1.6 [29]. The booklet also outlined how to meet physical activity recommendations of at least 150 mins/week of moderate intensity physical activity [30], 10000 steps per day [31] and restriction of sitting time to 3 hr/day or less [23,32].

Women with a baseline BMI in the overweight range (25–29.9 kg/m^2^) were advised to lose up to 7% of baseline weight (an amount shown in previous interventions to have significant clinical outcomes for the overweight) [33]. Written advice was provided in booklet format to meet the same RDIs as the healthy weight women, within a maximum energy intake of 6300 kJ/day, which is 2000 kJ less than the estimated requirement for weight maintenance of 8300 kJ [29] in order to achieve a weight loss of approximately 0.5 kg per week. Physical activity advice was increased to 250 mins/week of moderate intensity to help achieve weight loss [34], with the same daily step count and sitting time as the healthy weight group.

A protocol responding to changes in BMI category was developed. It stated that, if in achieving their weight loss goal the overweight women achieved a BMI in the healthy weight range, they were advised to maintain that new weight within 1 kg for the remainder of the study and would be given the written booklet containing advice prepared for healthy weight women. Conversely, any healthy weight women found to have gained sufficient weight to be reclassified as overweight would be given the written advice and behavioural goals for the overweight women, and advised to lose weight to re-attain the healthy weight range. The process for change in goals is shown in the Figure in Additional file 1.

### Sample size

The sample size calculation was based on the main outcome measure of body weight. Observational studies of women in this age group in the Australian population have demonstrated a mean (SD) weight gain of 1.04 (4.7) kg over a two-year period [22]. Given both intervention groups were comprised of equal numbers of healthy weight and overweight women and presuming the overweight women would meet the intervention goal of losing 5 kg^a^ in the first 12 months and the healthy weight women would show zero weight change, the net weight change should be a 2.5 kg weight loss in the MI group by the end of phase 1. Based on the Australian data of net weight gain in the general population of mid-age women managing their weight by self-directed means [21], we would expect a mean (SD) net weight gain of 0.5 (4.7) kg per year in our SDI (control) group. This would give an expected difference between the two groups of 3.0 kg after 12 months (end phase 1) and 3.5 kg after 24 months (end phase 2). Assuming equal sample sizes, to detect a difference in weight between groups of 3.5 kg with 80% power and a significance level of 0.05, a sample size of 22 women was required for each group. Allowing for an attrition rate of 20% by the end of 24 months, a total sample size of 55 women is required.

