While there is a substantial body of evidence showing that weight loss in the obese reduces cardiovascular risk, the body of evidence on weight gain prevention interventions is scant [17], with only one RCT investigating whether weight gain prevention in pre-menopausal women can mitigate the increase in cardiovascular risk usually associated with menopause [18,19]. The Women’s Healthy Lifestyle Project conducted in the United States was designed to prevent weight gain and increased cardiovascular risk associated with menopause [18,19]. Pre-menopausal women (44–50 y, N = 535) randomized into a lifestyle intervention group (15-session diet and exercise education program followed by a maintenance program) lost on average 0.1 (5.2) kg after 54 months compared with a gain of 2.4 (4.9) kg in the assessment-only group [19]. While the trial showed that it was possible to prevent menopausal weight gain and to limit the typical post-menopausal rise in low density lipoprotein (LDL) cholesterol, the researchers acknowledged that the 15-session intervention held over 20 weeks was labour intensive and required a substantial time commitment from participants [20]. There is a need for the development of less intensive interventions that could feasibly be implemented on a population basis.

While women are known to attempt weight control (defined as weight maintenance for those of healthy weight and weight loss for the overweight) [21], self-directed efforts have not prevented population weight gain. Data from over 12,000 mid-age women in the population-wide Australian Longitudinal Study on Women’s Health showed 70% of participants reported behaviours aimed at losing weight or preventing weight gain, but they were mostly unsuccessful [21]. In the first two years of the study, the women without surgical menopause gained a mean (SD) of 1.04 (4.7) kg [22], and the cohort continued to gain weight at 0.5 kg/year over the next three years [23]. In a study of the weight control practices used by the women [21] the only group who managed to successfully prevent weight gain included a commercial program in addition to the typical public health strategies of 'cutting down on the size of meals and snacks plus cutting down on fats and sugars plus exercise’. This demonstrates the need for population based interventions that provide the face-to-face support typical of commercial programs, in addition to the more traditional awareness raising and education strategies.

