### Data analysis

Outcome measures collected at baseline will be compared to those at 12 months (after adjusting for baseline weight) to assess intervention effects and compared with measures at 24 months (end phase 2) to assess whether the intervention effects were maintained. Analyses will be conducted using the intention to treat principle, and performed using SPSS version 19 (IBM). All variables will be checked for plausibility. Continuous variables will be assessed for normality. Independent sample t-tests and chi-squared tests will be conducted on continuous and categorical variables (respectively) to check they do not vary by intervention group at baseline, and by completers versus attriters. Analysis of covariance will be used to examine whether the intervention groups differed significantly in weight at each of 12 and 24 months after adjusting for baseline weight. Behaviour changes in diet and physical activity will be assessed as secondary outcome measures using analysis of covariance to determine whether the MI and SDI groups differed significantly in dietary or physical activity behaviours at 12 months. Results will be stratified for baseline BMI category.

Logistic regression analysis will be performed to assess whether categorical variables, such as smoking status significantly influenced weight. The visceral adipose tissue variable will be assessed for between group differences at 12 and 24 months using independent sample t-tests, and analyses stratified by BMI category to determine whether the results differed for the healthy weight and overweight women. Sensitivity analyses will be conducted to determine the effects on the outcomes of different methods of treating loss to follow-up (last observation carried forward versus imputation). The relationship between weight outcomes and compliance with the diet and physical activity behaviours will be assessed using mediation analysis [55].

A per protocol analysis will be conducted on women who adhered to the requirements of their assigned group. Adherent women are defined as those who completed all required eating and physical activity diaries over the 12-month period and attended all assessment sessions, regardless of assigned group, and who attended all five health professional consultations for the MI group. Results of the protocol adherent group will be compared with non-adherers in each group, that is, those who did not meet the adherence recommendations.

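### The sizing takes the MI mean from a half-and-half mix of 5 kg and 0 kg losses but states no MI-arm SD; if 4.7 kg is the spread within a BMI category, power at 22 per group falls by about 5 to 6 points

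*Protocol article*

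**What the plan says.** The Sample size section of the protocol article takes a two-year weight change with SD 4.7 kg from an observational study of women of this age. It applies that SD to the control arm only: "we would expect a mean (SD) net weight gain of 0.5 (4.7) kg per year in our SDI (control) group". The MI mean is built from two equal halves. Overweight women lose 5 kg, and "the healthy weight women would show zero weight change, the net weight change should be a 2.5 kg weight loss in the MI group". The expected differences are 3.0 kg at 12 months and 3.5 kg at 24 months. The calculation is made "to detect a difference in weight between groups of 3.5 kg" and concludes "with 80% power and a significance level of 0.05, a sample size of 22 women was required for each group". Adding 20% attrition gives a total of 55. Neither the sidedness of the test nor an MI-arm SD is stated.

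Randomisation is stratified by BMI category. The Data analysis section plans the primary test as follows: "Analysis of covariance will be used to examine whether the intervention groups differed significantly in weight at each of 12 and 24 months", adjusting for baseline weight. It adds that results will be stratified by baseline BMI category, but names neither category nor a group-by-category term in the primary model.

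**The concern.** A mean taken from a mixture brings the mixture's spread with it. The plan carries the average of 5 kg and 0 kg into the expected difference, but nothing shows that the 2.5 kg spread between the two halves entered the MI-arm variance. The cohort that supplied 4.7 kg had no category-specific weight goals, so there is no reason to expect its SD to contain that spread.

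At stake is the 80% power attached to 22 per group. The Discussion relies on it when it calls the study sufficiently powered for weight differences according to the category goals, and those goals are where the extra spread comes from. A null result could be over-read, more so at 12 months, where the assumed difference is smaller.

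**Working it through.** **Inputs, all from Sample size:** differences 3.5 kg (24 months) and 3.0 kg (12 months); SD 4.7 kg; MI category means −5 and 0 kg in equal halves; one SDI gain with no category split; 22 per group; level 0.05; attrition 20%.

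**1. The plan's own figure.** Normal formula, n per group = (SD_MI² + SD_SDI²)(z_α + z_0.80)²/δ². With 4.7 kg in both arms the variances sum to 44.18.
- One-sided: 44.18 × 6.183 / 12.25 = 22.3.
- Two-sided: 44.18 × 7.849 / 12.25 = 28.3.

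So 22 is reproduced, within rounding, only by a one-sided test. Attrition checks: 44 / 0.80 = 55.

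**2. The MI-arm SD implied by the mixture.** Assume 4.7 kg is the SD within a category. MI variance = 4.7² + 0.5 × 0.5 × 5² = 22.09 + 6.25 = 28.34, so the SD is 5.32 kg. For the MI arm as a whole to have SD 4.7 kg, its within-category SD would have to be √(22.09 − 6.25) = 3.98 kg.

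**3. Power at 22 per group (noncentral t, 42 df).** The standard error of the difference is 4.7√(2/22) = 1.417 kg with a common SD, and √((28.34 + 22.09)/22) = 1.514 kg with the mixture. For 3.5 kg the noncentrality falls from 2.47 to 2.31; for 3.0 kg it falls from 2.12 to 1.98.

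| Within-category SD | MI SD | SDI SD | 3.5 kg, one-sided | 3.5 kg, two-sided | 3.0 kg, one-sided | 3.0 kg, two-sided |
|---|---|---|---|---|---|---|
| no mixture added | 4.70 | 4.70 | 78.4% | 67.5% | 66.9% | 54.3% |
| 4.7 in both arms | 5.32 | 4.70 | 73.5% | 61.7% | 62.0% | 49.1% |
| 4.2 in both arms | 4.89 | 4.20 | 80.5% | 70.2% | 69.3% | 56.9% |

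In the second row the sample size formula gives 50.43 × 6.183 / 12.25 = 25.5 per group one-sided, or 50.43 × 7.849 / 12.25 = 32.3 two-sided.

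**4. Splitting the two-sided gap.** From 80% to 67.5% is 12.5 points, present before any mixture variance is added. From 67.5% to 61.7% is 5.8 points, due to the mixture.

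**5. What the planned ANCOVA recovers.** Scenario: the second row of the table, 3.5 kg, simulated with assumed baseline weights. Two-sided power is about 62.7% adjusting for baseline weight only, 63.3% adding category, and 65.6% adding group × category. One-sided, it rises from about 75% with weight only to about 77–78% with the interaction. Baseline weight alone leaves most of the mixture spread in the residual, because that spread exists in one arm only.

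**The case against.** The strongest objection is that 4.7 kg is never called a within-category SD. It is the overall SD of change in a cohort, and this trial excludes obese women and several diagnoses, so its spread could differ in either direction. This stands. A reader might infer that the plan's assumed means by themselves rule out 80% power even one-sided. They do not: the plan's own inputs reproduce 22 one-sided within rounding, and a within-category SD near 4.2 kg in both arms gives 80% one-sided with the mixture included. What remains is that the section gives 4.7 kg to an SDI arm with the same BMI mix and a single assumed gain. If the SDI categories move alike, 4.7 kg is their within-category spread. That makes the assumption consistent with the section, though not stated in it.

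A reader might also take the earlier US trial in the Background as confirmation, since its intervention group "lost on average 0.1 (5.2) kg after 54 months compared with a gain of 2.4 (4.9) kg in the assessment-only group". Those SDs are for change over 54 months and cannot stand in for SDs at 12 or 24 months. The two arms' SDs also imply an added component of only √(5.2² − 4.9²) = 1.7 kg, not 2.5 kg.

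The analysis could remove the category spread, since randomisation and reporting are both stratified by category. This stands in part: the stratified results do not commit the pooled primary test to a group-by-category term, and that term does most of the recovering.

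Finally, the effect is modest, and one common SD is an ordinary simplification. That is fair, and it limits the weight of the point. It does not excuse leaving the MI-arm SD unstated when the section itself specifies the mixture.

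**Conclusion.** The concern holds in conditional form. The sizing builds the MI mean from two categories 5 kg apart, gives no MI-arm SD, and borrows its only SD from a cohort without category goals. If 4.7 kg is the spread within a category in both arms, power at 22 per group for 3.5 kg is 4.9 points lower one-sided (73.5% against 78.4%) and 5.8 points lower two-sided (61.7% against 67.5%). For 3.0 kg at 12 months it is 62.0% against 66.9% one-sided, and 49.1% against 54.3% two-sided.

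These figures rest on an equal category mix, the stated category means, no further variation in individual response, and an unadjusted comparison. The larger part of the two-sided shortfall comes from the unstated sidedness, which is a separate issue. The documents do not support the claim that 80% is unattainable one-sided, nor a case for enrolling more women on this ground.

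**What to change.** **Sample size section.** State the SD assumed for each arm and whether the test is one- or two-sided. Replace the single 80% with a range for 22 per group: about 74–78% one-sided and 62–67.5% two-sided for 3.5 kg, with about 62–67% and 49–54% for 3.0 kg alongside. Say that the lower ends take 4.7 kg as the within-category SD and the upper ends take 4.7 kg as the overall SD in both arms. Do not use the 54-month SDs from the Background as replacement inputs. Bring the Discussion's statement on sufficient power into line.

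**Data analysis section.** Add BMI category, which is the randomisation stratum, and a centred group × category term to the primary ANCOVA. Report the MI–SDI difference averaged over the two categories. This takes the mixture variance out of the residual and recovers about 2 to 4 points of power.

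**Cost.** A less favourable power statement, two degrees of freedom, and no new data. Recruitment is complete with 54 women randomised, and enrolment does not change.

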### Outcome measures

Outcome measures were assessed for all participants at baseline, between May-September 2010, and reassessed at 3, 12, 18 and 24 months (end of monitoring phase 2) as shown in Additional file 3. The primary endpoints are at 12 months to determine the effects of the intervention and at 24 months to assess whether the intervention effects were maintained. Weight was the primary outcome measure.

#### **
*Measurement procedure*
**

Assessments were conducted in the early morning, in the anthropometry laboratory at the University of Newcastle (Australia). Procedures and protocols for the measurements were standardised, documented, and research assistants were trained in their application prior to collection. Participants fasted overnight, and upon entry to the laboratory removed their shoes and excess clothing. The assessment process lasted approximately 60 minutes for each participant, and they were provided with breakfast prior to leaving the laboratory.

#### **
*Anthropometry*
**

Height was measured using a stadiometer (Surgical and Medical Products) correct to 0.1 cm using the stretch stature method. Weight and body composition (percentage fat, skeletal muscle mass) were measured at all time points using BIA Omron HBR-500 Body Composition Monitor with Scales correct to 0.1 kg. BMI was calculated using the standard equation (weight [kg]/height[m]^2^). Waist circumference was collected as a valid marker of central adiposity [44] using a non-extensible steel tape to measure at the level of the mid-point between the lower costal border and the iliac crest (KDS F10-02, KDS Corporation, Osaka, Japan). Two measures were collected and averaged. Visceral adipose tissue area was estimated using the InBody720 Body Composition Analyzer (Biospace) at 12, 18 and 24 months.

#### **
*Biomarkers of metabolic syndrome*
**

Thirty millilitres of blood was collected from each participant by a trained phlebotomist and analysed by a laboratory accredited with the National Association of Testing Authorities Australia. Fasting measures of total cholesterol, low density lipoprotein cholesterol, high density lipoprotein cholesterol, triglycerides and glucose were assessed. Blood samples have been stored in a -80°C freezer for further analyses (sex hormones, insulin, leptin, and antioxidants to validate dietary intake) should funds become available.

#### **
*Blood pressure and resting heart rate*
**

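### The 22 women per group reproduce only under an undeclared one-sided 5% test; an unadjusted two-sided test gives about 67–70% power for 3.5 kg

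*Protocol article*

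**What the plan says.** The Sample size section bases the calculation on body weight. It cites cohort data that "have demonstrated a mean (SD) weight gain of 1.04 (4.7) kg over a two-year period" and carries the same SD to the control arm: "we would expect a mean (SD) net weight gain of 0.5 (4.7) kg per year in our SDI (control) group". No other SD appears. The expected between-group difference is 3.0 kg at 12 months and 3.5 kg at 24 months. The calculation uses the larger and gives its result per group: "a difference in weight between groups of 3.5 kg with 80% power and a significance level of 0.05, a sample size of 22 women". With 20% attrition by 24 months, the total is 55.

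The Outcome measures section makes both time points primary: "The primary endpoints are at 12 months to determine the effects of the intervention and at 24 months" for maintenance of effect. The Data analysis section plans analysis of covariance on weight at each time point, adjusted for baseline weight, to see whether the groups differ significantly. It names no direction. The Discussion concedes low power for secondary outcomes but describes the study as adequately powered for weight.

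**The concern.** A significance level of 0.05 given without qualification is normally read as two-sided, and the planned group comparison fits that reading. On that reading 22 per group is too few for the stated power. The total of 55 and the Discussion's assurance about power for weight both rest on this figure.

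The stake is interpretation. If a true 3.5 kg difference would be missed about one time in three, rather than one in five, a non-significant result says less against the intervention than the article suggests. The findings are also meant to inform a larger trial. The 12-month endpoint, where a smaller difference is expected, has no power statement at all.

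**Working it through.** **Inputs (Sample size section).** Difference d = 3.5 kg at 24 months and 3.0 kg at 12 months; SD = 4.7 kg, assumed common to both arms and both time points because no other SD is given; significance level 0.05; power 80%; equal groups; 20% attrition. Sidedness is not stated, so both cases are run.

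**1. Reproducing the printed figure.** Normal formula: n per group = 2 × (z_α + z_β)² × (SD/d)², with (4.7/3.5)² = 1.803.
- One-sided 5%: 2 × (1.645 + 0.842)² × 1.803 = 22.3. This matches 22 to the nearest whole number. The t distribution gives 23.0.
- Two-sided 5%: 2 × (1.960 + 0.842)² × 1.803 = 28.3, so 29. The t distribution gives 29.3, so 30.
- Attrition: 44/0.8 = 55, as printed.

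The attrition step is right. The 22 follows only from the one-sided test.

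**2. Power at 22 per group for 3.5 kg.** The standard error is 4.7 × √(2/22) = 1.417 kg, and 3.5/1.417 = 2.470.
- One-sided: Φ(2.470 − 1.645) = 79.5%; noncentral t 78.4%.
- Two-sided: Φ(2.470 − 1.960) = 69.5%; noncentral t 67.5%.

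The smallest difference detectable with 80% two-sided power is about 4.1 kg (t distribution; 2.802 × 1.417 = 3.97 kg by the normal formula).

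**3. Size needed for 80% two-sided power at 3.5 kg.** 29 to 30 per group: 58/0.8 = 72.5, so 73, or 60/0.8 = 75 in total.

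**4. What baseline adjustment would have to supply.** For 80% two-sided power at 22 per group the SD would have to be about 4.05 kg (t) or 4.14 kg (normal). In the covariance analysis the residual SD is 4.7 × √(1 − r²), where r is the correlation of baseline weight with weight change. The article gives no r, so a range is shown.

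| r (assumed) | Residual SD, kg | Two-sided power, 22 per group, 3.5 kg |
|---|---|---|
| 0 | 4.70 | 67.5% |
| 0.3 | 4.48 | 71.6% |
| 0.4 | 4.31 | 74.9% |
| 0.5 | 4.07 | 79.6% |

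**5. The 12-month endpoint (3.0 kg, SD 4.7 kg, unadjusted).** Two-sided power at 22 per group is 54.3% (t) or 56.2% (normal). A one-sided test gives 66.9% or 68.2%. For 80% two-sided power, 39 to 40 per group are needed.

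**6. Using the randomised numbers.** With all 28 and 26 women evaluable, unadjusted two-sided power (t) is 76.5% for 3.5 kg and 63.3% for 3.0 kg.

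**The case against.** The strongest defence is that the article never says the test is two-sided. Its hypotheses are directional (loss with motivational interviewing, gain in the control group), and a one-sided 5% test returns both the 22 and, within rounding, the 80%. A reader might therefore go too far in calling this a plain arithmetic error, or in saying that the trial cannot have the power it claims. The documents do not support that: the figures agree with each other under one choice of test. What remains is that this choice is not declared and that the analysis section does not describe it.

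A reader might also infer that baseline adjustment cannot account for 22 because 4.7 kg is already the SD of a change. That is wrong. Adjustment lowers the residual SD whenever baseline weight correlates with change, and some correlation is plausible because the weight goals differ by BMI category. But about 0.5 would be needed, and the article neither states a correlation nor says that one was used.

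Finally, one might read the 80% as a claim about 12 months too. The sample size statement attaches it only to the 24-month difference of 3.5 kg, so the 12-month point is a gap in coverage and not a misstated figure. The 54% also uses the number left after 24 months' attrition; fewer losses by 12 months would raise it, to 63% at most on the randomised numbers.

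It is also fair to say that the trial is presented as a test of feasibility and preliminary effectiveness. That limits the consequence but does not make the stated power right.

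**Conclusion.** The point holds in this form. As printed, 22 per group with 80% power depends on a one-sided 5% test that the article does not declare. Under the two-sided reading that fits the planned comparison, power for 3.5 kg is about 67–70%, and 80% would need 29 to 30 per group. These figures assume SD 4.7 kg in both arms, 22 evaluable women per group and no variance reduction from adjustment. A correlation of about 0.5 would close the gap, but none is stated. Even full follow-up of the 28 and 26 randomised women leaves unadjusted two-sided power below 80%.

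Separately, the 12-month primary endpoint was not covered by the calculation. Its unadjusted two-sided power for 3.0 kg is about 54% at 22 per group and 63% with everyone evaluable. The Discussion's general statement of adequate power for weight is therefore not supported at either time point without assumptions that the article does not give.

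**What to change.** Keep the sample and correct the text.

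- State that the test is two-sided at 5%.
- Replace the 80% with about 67–70% for 3.5 kg at 24 months with 22 evaluable women per group, labelled as unadjusted, and add that about 4.1 kg is detectable with 80% power.
- Note that 80% for 3.5 kg would have needed 29 to 30 per group, or 73 to 75 in total after 20% attrition.
- Show any gain from covariance adjustment only beside the correlation assumed for it and the source of that value.
- Report 12-month power for 3.0 kg alongside: about 54% at 22 per group, 63% with all 28 and 26 evaluable.
- In the Discussion, replace the statement of adequate power for weight with one that conclusions rest on the estimated difference and its 95% confidence interval, as preliminary effectiveness.

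The cost is a few sentences and a less favourable power figure. No further participants and no change to the planned analysis are needed.
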